Despite its widespread use, the empirical evidence supporting the efficacy and specificity of extended testing time remains limited. While existing findings suggest that extended time can benefit students under time pressure conditions, it is not exclusive to those with ADHD as it also helps students without academic difficulties [17]. This raises important questions about the validity and fairness of such accommodations as specialists argue that valid accommodations must produce significantly greater improvements for the target group compared to those not eligible for the accommodation [18,19].

A systematic review of educational accommodations for children and adolescents with ADHD found 9 studies evaluating the effectiveness of extended time [17], but they exhibited significant methodological limitations that warrant important consideration. First, only 2 of them had experimental designs [20,21]. Second, they were all carried out in the United States and relied on predominantly White samples. Third, most were conducted before 2007, the most recent one having been published 10 years ago [22]. When we look at studies focusing on the college population, we find that they are both scarce and inconsistent, varying in study design [23,24]. Furthermore, again, the existing research has been conducted exclusively in the United States, limiting the generalizability of findings to diverse educational systems and cultural contexts. These methodological gaps highlight the need for more robust research to determine whether extended testing time achieves its intended purpose. Considering the cognitive heterogeneity of individuals with ADHD [25], a variance in response to the accommodation within the clinical group is also possible—which has also not been addressed by previous studies. Another important aspect is determining how much extra time should be provided. Today, this decision is grounded in common sense reasoning.

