Given these gaps, this study aims to assess the impact of additional test time on the performance of college and college-prospective students with and without ADHD. Using an experimental design, we will vary extended time conditions (25% and 50% extra time). We hypothesize that the performance of students of both groups will be superior when additional time is provided but that students with ADHD will potentially experience greater relative benefits. We anticipate that students’ performance will improve significantly more with 50% extra time. Furthermore, we hypothesize that students with ADHD who present greater cognitive and functional deficits will derive greater benefits from extended time accommodations.

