### Statistical Analysis

Primary performance analyses will use standardized, IRT‑equated scores from the ENEM‑based exams; raw counts will not be analyzed. Estimated marginal means with 95% CIs will summarize group profiles and within‑person gains. We will also conduct a sensitivity analysis excluding medicated individuals.

Group comparisons at each time limit (40, 50, and 60 minutes) will be performed using Welch *t* tests with Cohen *d* and 95% CIs. Within‑group time effects will be evaluated via repeated‑measure ANOVA with time (40, 50, and 60 minutes) as a within‑subject factor; the Mauchly test will assess sphericity, and Greenhouse-Geisser corrections will be applied when necessary. Planned paired contrasts (50 vs 40 and 60 vs 40 minutes) will use Bonferroni adjustment, and partial η^2^ will index omnibus within‑subject effects.

To directly test whether extended time benefits participants with ADHD more than controls, we will fit a linear mixed‑effects model with a random intercept for participant, coding time continuously in minutes (40, 50, and 60) so slopes are interpretable per minute. Fixed effects will use Satterthwaite df, and interaction tests will be corroborated with likelihood ratio comparisons under maximum likelihood.

Assumptions will be examined using Shapiro-Wilk tests and *Q*-*Q* plots (normality), Levene tests (homogeneity), and visual inspection of mixed‑model residuals. When ANOVA assumptions are not met, inference will prioritize mixed‑model results. Analyses will be conducted in R (*lme4* and *lmerTest*, *emmeans*, and *afex* packages; R Foundation for Statistical Computing).

Missing data will be handled using multiple imputation under the assumption that data are missing at random, and all analyses will be conducted on the imputed datasets using an intention‑to‑treat approach.

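### The group-by-time test uses a random intercept only, so its standard error is too small if participants differ in how much they gain from extra time

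*Protocol article*

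**What the plan says.** All of the following is in the protocol article.

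- **Methods, Statistical Analysis, the headline test.** "To directly test whether extended time benefits participants with ADHD more than controls", the plan fits a linear mixed "model with a random intercept for participant". Time is continuous (40, 50, 60), "so slopes are interpretable per minute". Fixed effects use Satterthwaite degrees of freedom, and "interaction tests will be corroborated with likelihood ratio comparisons under maximum likelihood". No random slope, other within-person covariance or robust standard error is named.
- **Same section, within-group analyses.** A repeated-measures ANOVA is run in each group. Mauchly's test checks sphericity, and Greenhouse-Geisser "corrections will be applied when necessary".
- **Same section, assumptions paragraph.** After listing checks of normality, homogeneity and mixed-model residuals, it continues: "When ANOVA assumptions are not met, inference will prioritize" the mixed-model results.
- **Introduction.** The authors note that "a variance in response to the accommodation within the clinical group is also possible", and they hypothesise that "students with ADHD who present greater cognitive and functional deficits will derive greater benefits from extended time accommodations".

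**The concern.** A random intercept alone implies compound symmetry: equal variances and equal correlations across the three time limits, and one true slope shared by everyone in a group. The Introduction expects gains to differ between students with ADHD, so the confirmatory model assumes away something that the protocol predicts.

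With three equally spaced times, each person supplies two within-person contrasts, one linear and one quadratic. The random-intercept model pools both into a single residual variance. Slope variation enters the linear contrast only, and that is the contrast that carries the group-by-time effect. Pooling it with the quieter quadratic contrast gives a standard error that is too small, on about 2N degrees of freedom instead of about N.

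The likelihood ratio comparison is no safeguard if both nested models keep the same random-effects structure, because both then share the misspecification. At stake is the error rate of the only stated direct test of whether extended time helps students with ADHD more than controls.

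**Working it through.** **The plan's own figures.** The article gives no residual variance, slope variance or operating characteristics for this model, so there is no stated figure to reproduce for the interaction test. The one design calculation, in Sample Size Calculation, supplies the group sizes. For a paired comparison at d = 0.45 and two-sided 5% (sidedness assumed), n = ((1.960 + 0.842)/0.45)² = 38.8. Noncentral-t power is 0.793 at n = 40, so 40 per group reproduces to rounding.

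**Inputs**
- Group sizes: 40/40 planned (Sample Size Calculation); 60 ADHD and 43 control enrolled (Results, Overview).
- Times 40, 50 and 60, so the sum of squared centred minutes is 100 + 0 + 100 = 200.
- Assumed, not in the article: residual SD s = 0.5, and SD of the true 20-minute gain g = 0.25, 0.5, 0.75 or 1.0. Only the ratio matters, through λ = g²/(2s²) = 0.125, 0.5, 1.125 and 2.

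**Formula, equal variation in both groups.** An observed 60-minus-40 gain has true variance 2s² + g². The model works with 2s² + g²/2. Hence

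model SE / true SE = √[(1 + λ/2)/(1 + λ)], and type I error ≈ 2·[1 − Φ(1.96 × that ratio)].

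Example, g = 1.0: true variance 0.5 + 1.0 = 1.5; model variance 0.5 + 0.5 = 1.0; SE ratio √(1.0/1.5) = 0.816; type I error 0.110. As λ grows the ratio tends to 1/√2 = 0.707 and the error to 0.166.

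**Formula, variation in the ADHD group only** (n₁ ADHD, n₀ control, N in total, variances in units of the residual variance).
- True variance of the difference: (1 + λ)/n₁ + 1/n₀.
- Model variance: {[(n₁ − 1)(1 + λ) + (n₀ − 1) + N]/(2N − 2)} × (1/n₁ + 1/n₀).

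Example, λ = 2 at 60/43: true 3/60 + 1/43 = 0.0733; pooled residual (59×3 + 42 + 103)/204 = 1.578; model 1.578 × 0.0399 = 0.0630; SE ratio √(0.0630/0.0733) = 0.927; type I error 0.069.

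**Type I error of the planned test** (analytic; 40,000 simulated trials per cell agree to within about 0.3 percentage points)

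| Gain SD | λ | Both groups vary (either size) | ADHD only, 40/40 | ADHD only, 60/43 |
|---|---|---|---|---|
| 0.25 | 0.125 | 5.7% | 5.4% | 5.2% |
| 0.5 | 0.5 | 7.4% | 6.3% | 5.7% |
| 0.75 | 1.125 | 9.4% | 7.6% | 6.3% |
| 1.0 | 2 | 11.0% | 9.0% | 6.9% |

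**Alternatives in the same simulations.** A Welch test on per-person slopes or gains stays at 4.8-5.1% in every cell. A pooled t test on per-person slopes, which is the balanced-data equivalent of a random slope with one common variance, also holds 5% when both groups vary equally. With ADHD-only variation at 60/43 it is conservative: 4.7% falling to 3.3%.

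**Direct REML fits** (150 runs, 40/40, λ = 2, both groups varying, time in 10-minute units). Empirical SD of the interaction estimate 0.260; mean random-intercept SE 0.221; mean random-slope SE 0.271; rejection 10.7% against 6.0%.

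**Boundary cases.** With no slope variance the planned test holds 5.0%. If the extra variance lies only in the quadratic contrast (there doubled, λ = 0), the planned SE is too large and the test rejects 1.7%.

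**The case against.** Four points can fairly be made against this.

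1. **The size is assumed.** The article gives no variances, the inflation is nil without slope variance, and the direction can reverse. This stands. The table is a range, not an estimate for this trial.
2. **The protocol's hypothesis concerns the ADHD group, not both.** On that reading the inflation is modest at the enrolled sizes, 5.2-6.9%. This also stands. The 11% figure needs equal variation among controls, which the article neither predicts nor excludes.
3. **A reader might infer that the plan falls back on the random-intercept model exactly when sphericity fails, and so discards the robust result when it is most needed.** The article does not support this. Sphericity has its own remedy, Greenhouse-Geisser. The priority sentence comes later, after normality, homogeneity and residual checks, and it neither names sphericity nor excludes it. It also bears on the within-group ANOVA, whereas the group-by-time test uses the mixed model in every case. Giving priority is not discarding, and the Bonferroni-adjusted paired contrasts remain. What is left is an ambiguity: if sphericity were read into the sentence, a result corrected for non-sphericity would yield to a model that itself assumes compound symmetry.
4. **The per-minute slope was a deliberate choice.** A random slope, or per-person slopes, keeps it, so there is no need to move to time as a factor.

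That the analysis plan might add a random slope is not a full answer, because the article does fix a random-effects structure.

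**Conclusion.** The point holds in a conditional form. The only stated test of differential benefit rests on a model that allows no person-to-person variation in gain, although the protocol expects such variation. If linear gains vary, the interaction SE is too small, by a factor of at most about √2. Under the assumed residual SD of 0.5 and gain SD of 0.25 to 1.0, type I error is about 5.5-11% if both groups vary equally. With ADHD-only variation it is about 5-9% at 40/40 and 5-7% at 60/43. These figures assume complete, balanced data, normal errors and slope variation that is linear in time.

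It would go too far to say that the test is inflated regardless of the data, or that the plan prescribes the weaker model whenever sphericity fails. The first depends on an unknown variance, and the second is unclear wording.

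**What to change.** 1. Add a by-participant random slope for time to the group-by-time model. It is estimable with three exams per person and keeps the per-minute interpretation. Alternatively, compute each participant's slope, or the 60-minus-40 and 50-minus-40 gains, and compare the groups with a Welch test. The Welch test also allows unequal variances by group, which matters if mainly the ADHD group varies and the groups are 60/43.
2. Keep the richer random-effects structure in both models of the likelihood ratio comparison.
3. Report the random-intercept model alongside and date the change, because Results, Overview says that analysis began in March 2026.
4. Add a sentence saying that the priority given to mixed-model results does not displace the Greenhouse-Geisser result when sphericity fails.

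The cost is a few lines of R and about two sentences of text. Intervals will be slightly wider if slopes vary, and the denominator degrees of freedom fall from about 2N − 2 to N − 2 (204 to 101 with 103 participants), which is of little consequence at this size.

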#### Intervention Procedures

To minimize fatigue, the intervention will be administered on a separate day from the psychiatric and neuropsychological assessments in groups of 5 to 15 participants and will always be administered in the morning. To assess participants’ optimal performance, they will be instructed to take medications as usual. Information regarding dose and time of intake will be collected on the day of the intervention. Each session will be facilitated by at least one assistant and the principal investigator (PI). Sessions will be conducted in quiet university or preparatory school classrooms to maintain a naturalistic environment.

Each participant will complete an academic exam with 3 different versions (A, B, and C) of similar difficulty and length. Each version will be paired with 1 of 3 distinct time conditions: 40 minutes (standard), 50 minutes (25% extra time), and 60 minutes (50% extra time). To control for potential confounding variables and ensure that the results are not biased by the order of conditions or exam versions, both the sequence of the exam versions and the time conditions will be randomized for each participant, as illustrated in Figure 1. This counterbalanced design ensures that each participant experiences all 3 time conditions (40, 50, and 60 minutes) and each exam version (A, B, and C) in a different order, preventing any systematic influence from order effects on the outcomes. Sequences of task orders will be computer generated using a random number generator and then counterbalanced so that each condition appears equally often in each position across participants.

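### The only between-group test of benefit codes time as a straight line, so the ADHD-specific effect of 25% extra time gets no between-group test

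*Protocol article*

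**What the plan says.** The Introduction makes the amount of extra time part of the question: "we will vary extended time conditions (25% and 50% extra time". The abstract's conclusions also present effectiveness at different amounts of extra time as a contribution of the study. Intervention Procedures sets the conditions as "40 minutes (standard), 50 minutes (25% extra time), and 60 minutes (50% extra time"), which are equally spaced.

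Statistical Analysis gives one model the task "To directly test whether extended time benefits participants with ADHD more than controls". It is a linear mixed model "with a random intercept for participant, coding time continuously in minutes (40, 50, and 60) so slopes are interpretable per minute", and its "interaction tests will be corroborated with likelihood ratio comparisons under maximum likelihood". No factor-coded time, quadratic term or check of linearity is stated.

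The 50-minute condition is handled separately in three other places in that section:

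- "Group comparisons at each time limit (40, 50, and 60 minutes) will be performed using Welch" *t* tests.
- A repeated-measures ANOVA within each group, where "Planned paired contrasts (50 vs 40 and 60 vs 40 minutes) will use Bonferroni adjustment".
- Estimated marginal means with 95% CIs, given as a summary of group profiles and gains.

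**The concern.** The specificity question is whether the ADHD group gains more than controls. The Introduction itself says that a valid accommodation should help the target group significantly more than others. With two amounts of extra time under study, a reader will want that comparison at 25% as well as at 50%.

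The linear coding gives one number for both. It fixes the differential gain at 50 minutes to be half of that at 60, whatever the 50-minute scores show.

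The other analyses do not fill the gap. A Welch test at 50 minutes compares levels, so it mixes any group difference already present at 40 minutes with the gain. The 50 vs 40 contrasts are made within each group, and a significant result in one group but not the other is not a test of the difference between them. The marginal means are descriptive.

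**Working it through.** **Inputs.** From the article: limits of 40, 50 and 60 minutes (Intervention Procedures); 40 per group planned, *d* = 0.45, 80% power (Sample Size Calculation); 60 ADHD and 43 control participants enrolled (Results, Overview). Assumed, because the article does not give them: a residual SD of 0.5 (range 0.4 to 0.8), differential gains of up to 0.4 on the score scale, no gain in controls, and two-sided 5% tests.

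**1. The plan's own figure.** For a paired comparison within one group, (1.960 + 0.842)²/0.45² = 7.85/0.2025 = 38.8. That is 39 per group, or 78 in total. The paired *t* test needs 41, and 40 gives 79.3% power. So 80 is reproduced as a within-group size. The plan gives no figure for the between-group difference in gain. For a difference of 0.45 SDs of the gain, power is about 51% with 40/40 and 61% with 60/43.

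**2. Weight of each exam in the slope.** Centred time is (−10, 0, +10), with sum of squares 200. The weights are (−10, 0, +10)/200 = (−0.05, 0, +0.05), so the slope is (Y60 − Y40)/20. Generalised least squares under a random intercept gave the same weights at intraclass correlations of 0, 0.3, 0.6 and 0.9.

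**3. Check on simulated data (60/43).** The mixed-model interaction was 0.029928, and the group difference in (Y60 − Y40)/20 was also 0.029928. Adding 1.0 to every ADHD score at 50 minutes left the estimate at 0.029928. Only the standard error moved, from 0.00827 to 0.01078. The identity therefore holds for the estimate, not for the whole test statistic. It needs complete data, which imputation supplies, and no exam-version or order covariates; none are stated for this model.

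**4. What the slope can and cannot show.** 4,000 simulated trials per pattern, 60/43, SD 0.5:

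| Differential gain at (50, 60) | Slope difference per 10 min | Gain at 50 implied by the line | True gain at 50 | Power of the linear test |
|---|---|---|---|---|
| (0, 0.4) threshold | 0.20 | 0.2 | 0 | 79% |
| (0.2, 0.4) linear | 0.20 | 0.2 | 0.2 | 81% |
| (0.4, 0.4) plateau | 0.20 | 0.2 | 0.4 | 79% |

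Detection is unaffected by the shape, but the shape is lost.

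**5. What a direct contrast would give.** With time as a factor, SE of group × (50 vs 40) = √[2 × 0.5² × (1/60 + 1/43)] = √(0.5 × 0.03992) = 0.141, on 2 × (103 − 2) = 202 df (critical *t* 1.972).

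- Gain 0.4: 0.4/0.141 = 2.83, power about 80%. With Bonferroni for two contrasts (critical *t* about 2.26), 72%.
- Gain 0.2: 0.2/0.141 = 1.42, power about 29% unadjusted.
- Unadjusted power for a 0.4 contrast at other SDs: 94% at 0.4, 65% at 0.6, 42% at 0.8. The 0.6 case is nearest to the plan's *d*, since 0.4/(0.6 × √2) = 0.47.

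**6. Departure from linearity.** The contrast Y40 − 2·Y50 + Y60 has SE √(6 × 0.25 × 0.03992) = 0.245. Under the plateau its value is −0.4, so 0.4/0.245 = 1.63 and power is only about 37%.

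**The case against.** The strongest reply is that the planned test answers the question it was given. The hypotheses say that both groups improve, that ADHD may gain more, and that performance improves more with 50% extra time. None states a group difference at each extension separately. A one-degree-of-freedom trend test that puts its weight on the largest extension is a reasonable test of an overall differential benefit. That stands, and it is why the slope can remain the lead test.

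A reader might infer more than the article supports in three ways.

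- **That 25% extra time is never analysed.** It is: in the Welch tests, the within-group contrasts and the marginal means, where a plateau in one group could be seen. What is missing is only the between-group test of the gain.
- **That the linear test loses much power.** It does if the differential gain shrinks at 60 minutes. With gains of (0.4, 0.2) the linear test has 27% power against about 80% for the direct contrast. But the Introduction expects more improvement at 60 minutes, and for the three patterns tabulated above nothing is lost.
- **That factor coding in the ANOVA contradicts linear coding in the mixed model.** One is within-group and the other between-group, so they address different questions.

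Nor does the article say that a per-minute slope will be reported as the effect of 25% extra time.

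It is also fair to say that extra contrasts carry a multiplicity cost, and that a null result for a small 25% effect would be uninformative.

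**Conclusion.** The point holds in limited form and should be fixed. The interaction estimate rests on the 40- and 60-minute scores alone, exactly so with complete data, a random intercept and no covariates. The test is valid for an overall ADHD-specific benefit. It imposes a straight line, and it leaves the ADHD-specific gain from 25% extra time without any between-group test in a study that sets out to compare amounts of extra time.

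The algebra needs no assumption about variances. The power figures do: they depend on the assumed residual SD and range from 94% to 42% for a 0.4 contrast as the SD goes from 0.4 to 0.8. The documents do not support the stronger conclusion that the planned test is wrong for its stated purpose.

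**What to change.** Add to Statistical Analysis, or substitute, a mixed model with time as a three-level factor, group, their interaction and a random intercept.

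- Name one lead test: group × (60 vs 40), or the equivalent slope. With complete data the two give the same estimate up to the factor of 20, with virtually the same power.
- Report group × (50 vs 40) with its 95% CI as a secondary contrast. If both contrasts are used for inference, apply the plan's Bonferroni adjustment.
- At the least, add a test of departure from linearity. Its power is low (step 6), so the contrast with its interval is more informative.
- Keep the per-minute slope as a summary.
- Date the change relative to the March 2026 start of analysis, and say whether any interaction result had been seen.

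The planned R packages already do this and no new data are needed. The cost is a fall in power from about 80% to 72% for a 0.4 contrast if two are adjusted (SD 0.5, 60/43). Power for a 0.2 gain at 25% extra time is also low, about 29% unadjusted. A non-significant result there should therefore be read from its interval and not as evidence of no effect.

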#### Primary Outcome Measure Instrument

The primary outcome measure will be the weighted test scores of a standardized task specifically constructed for this study. The weighted test scores will be calculated using the 3-parameter IRT. IRT is a statistical modeling approach that links individuals’ ability levels to their likelihood of responding correctly to each item, incorporating parameters for item difficulty, discrimination, and guessing. The guessing parameter measures the likelihood of a student guessing the correct answer purely by chance based on number of answer choices, item design, test taker behavior, and empirical calibration from response data; the discrimination parameter measures how well a question differentiates between high-performing and low-performing students by calculating the correlation between a student’s performance on a specific question and their overall test performance; and the difficulty parameter measures how hard or easy a particular question is based on the percentage of correct responses from all students [47].

The standardized task was designed based on the Brazilian National High School Exam (ENEM), which was constructed using the 3-parameter IRT. In this study, we selected a guessing parameter below 0.2, a discrimination parameter above 2, and a 2:1 ratio (difficult to easy) difficulty parameter. These indexes allow us not only to construct an exam equivalent to the real-world scenario but also to have 3 different tests with the same difficulty level. Each version consists of 12 questions covering different areas of knowledge using identical items that appear in the original ENEM (see Multimedia Appendix 1).

We conducted a pilot exam with 30 students to verify whether the 3 versions of the task were equivalent. First, we examined normality regarding exam scores using the Shapiro-Wilk test. As we found a signal for a nonnormal distribution, we used a Friedman ANOVA to assess group differences and paired Wilcoxon signed-rank tests to compare the scores between each pair of exams (A vs B, A vs C, and B vs C). In addition, we used a Shapiro-Wilk test to assess the normality of the scores for each administration order. As the distribution was normal, we conducted a repeated-measure ANOVA to examine whether the order of administration affected the scores. We inspected paired differences between orders using paired 2-tailed *t* tests.

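### If the mixed-model fallback replaces the within-group ANOVA, its single linear time slope leaves 25% extra time without a test of its own

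*Protocol article*

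**What the plan says.** All of this stands in the Protocol article, Statistical Analysis, unless noted.

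- Within-group time effects use a repeated-measures ANOVA "with time (40, 50, and 60 minutes) as a within‑subject factor".
- Each dose has its own comparison with standard time: "Planned paired contrasts (50 vs 40 and 60 vs 40 minutes) will use Bonferroni adjustment".
- One mixed model is described. Its purpose is given as "To directly test whether extended time benefits participants with ADHD more than controls". It has a random intercept for participant, "coding time continuously in minutes (40, 50, and 60) so slopes are interpretable per minute".
- "Assumptions will be examined using Shapiro-Wilk tests" and Q-Q plots for normality, Levene tests for homogeneity, and visual inspection of mixed-model residuals. Sphericity is handled separately, by the Mauchly test and the Greenhouse-Geisser correction.
- The fallback rule is: "When ANOVA assumptions are not met, inference will prioritize" the mixed-model results.

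No mixed model with categorical time is named, and no rank-based or resampling alternative. The Primary Outcome Measure Instrument section says of the pilot scores by exam version: "As we found a signal for a nonnormal distribution". The same paragraph reports that scores by administration order were normal.

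**The concern.** The planned contrasts ask two questions: is there a gain with 25% extra time, and is there a gain with 50%? A model with one linear slope asks only one, whether the slope is zero. If a failed assumption check moves the within-group inference to that model, the null hypothesis changes as well as the method, and the two doses share one answer.

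The move also does not cure its trigger. A Gaussian random-intercept model assumes normal residuals with equal variance too.

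Dose is one of the trial's stated aims. The Introduction names the amount of extra time as an open question and predicts a significantly larger improvement with 50% extra time. A gain confined to 60 minutes could be reported as a gain at 50 as well, and a gain at 50 that is gone by 60 could be missed.

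**Working it through.** **Inputs.** From Sample Size Calculation: d=0.45, 80% power, alpha .05, 40 per group. From Results: 60 ADHD and 43 control participants enrolled. Assumed: two-sided tests, d in SDs of the paired difference, within-person correlation 0.5 with equal variances, complete data.

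**The plan's own figure.** For one paired comparison, n = ((1.960 + 0.842)/0.45)² = 38.8, so 39 by the normal approximation and 41 by the noncentral t. Power at n=40 is 79.3%. The 40 per group is therefore reproduced, and this supports reading d as the paired-difference effect. At the Bonferroni level of .025, power at n=40 is about 70%.

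**Algebra.** Centre time at 50 and write m40, m50 and m60 for a group's means. With complete data the slope is

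b = (−10·m40 + 0·m50 + 10·m60)/(100 + 0 + 100) = (m60 − m40)/20.

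- The 50-minute scores have weight zero in the estimate.
- 50 vs 40 is 10b = (m60 − m40)/2. 60 vs 40 is 20b = m60 − m40.
- t is 10b/(10·SE) = 20b/(20·SE) = b/SE for both.

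A fitted example with linear time and group-by-time terms gave 0.3445 (SE 0.0803) and 0.6890 (SE 0.1607), both with z = 4.288 and p = 1.8e-05. Bonferroni doubles both p values alike, so they stay equal.

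**Consequence, with Bonferroni (.025) on both methods.** A rough check for a gain of 0 at 50 and 0.45 at 60, n=40: the noncentrality is 0.45·√40 = 2.85 and the critical t on 158 df is about 2.26, so the rejection rate is about Φ(2.85 − 2.26) = Φ(0.59), or 72%. Simulation gives 70% to 71%, slightly lower because the misfit at 50 minutes inflates the residual variance.

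| True gain at 50, 60 | n in group | 50 vs 40 declared, linear slope | 50 vs 40 declared, planned contrast |
|---|---|---|---|
| 0, 0.45 | 40 | about 70% | about 2.5% |
| 0, 0.45 | 60 | about 88% | about 2.5% |
| 0, 0.30 | 40 | about 35% | about 2.5% |
| 0, 0.20 | 40 | about 16% | about 2.5% |
| 0.45, 0 | 40 | about 2% | about 69% |

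With a gain of 0.45 at both limits, the slope model estimates the 50-minute gain as 0.45/2 = 0.225. In the 0, 0.45 scenario at n=40, the rates are nearly unchanged at correlations of 0.3 and 0.7 and with skewed errors.

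**With time as a three-level factor** in the same random-intercept model (truth 0, 0.45; Bonferroni), 50 vs 40 is declared in 2.5% of trials, and power for 60 vs 40 is 72% at n=40 and 89% at n=60.

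**How often the switch would fire with normal, equal-variance data.** The article gives no trigger rule.

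- Three Shapiro-Wilk tests in one group, any rejection counts: 1 − 0.95³ = 14% if independent.
- Six Shapiro-Wilk and three Levene tests, any rejection counts: 1 − 0.95⁹ = 37% if independent. Simulation at within-person correlation 0.6 gives about 34%.

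**The case against.** A reader might infer that the plan commits itself to declaring 25% extra time effective on the strength of the slope. The text does not go that far. To prioritize mixed-model results is not to say that the paired contrasts are dropped or read off the slope, and a slope per minute is not in itself a claim about 50 minutes. This stands as a limit on the point. It does not remove it, because no other mixed model is described that could take priority for the within-group question.

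Some per-dose reporting remains: marginal means with confidence intervals, and Welch tests at each time limit. The Welch tests compare groups, so they do not test a within-group gain. The source model for the marginal means is not given; if it is the linear one, the gains are again tied in the ratio 1 to 2.

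Four further stronger readings should be resisted.

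- Shared normality is not the source of the error. With no gain at either dose the slope test keeps its level, even with skewed errors. The harm comes from forced linearity.
- Testing the slope at .05 against the contrast at .025 gives about 79% against 2.6% at n=40, but that mixes alpha levels.
- Higher trigger rates can be obtained by counting Mauchly, which Greenhouse-Geisser already handles, or by assuming item parameters and an ability estimator for the 12-item test. The article supports neither. Levene across groups is not an assumption of a one-group ANOVA either, so 34% is the generous end.
- The pilot does not show that the switch will fire, since its normality findings were mixed.

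The group-by-time test uses the mixed model in any case and is not changed by the switch.

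**Conclusion.** The point holds in conditional form. If the described mixed model replaces the ANOVA for within-group effects, 25% extra time loses its own test, and the substitute does not cure the assumption failure that called for it. The error exists only where the gain departs from linearity; if the gain is linear in minutes, nothing false is declared. A gain of exactly zero at 50 with the full 0.45 at 60 is an extreme case, and the false-declaration rate falls to about 35% and 16% for 60-minute effects of 0.3 and 0.2 at n=40. How often this would matter cannot be fixed from the article, because the trigger rule is unstated. A design with three time limits is nevertheless meant to reveal departures from linearity, so the fallback should not assume them away.

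**What to change.** Either of two wordings is enough.

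1. State that the Bonferroni-adjusted paired contrasts (50 vs 40, 60 vs 40) remain the within-group dose inference whatever the assumption checks show, with a bootstrap or sign-flip permutation of the paired differences as the check for nonnormality.
2. If a mixed-model fallback is wanted for these contrasts, fit time as a three-level factor and take the same two contrasts per group with the same Bonferroni adjustment. The existing random intercept was sufficient in the simulations, under equal variances and correlations; an unstructured covariance is optional.

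The linear slope can stay for the group-by-time test.

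The cost is a sentence or two and a few lines of R, with no new data. Factor time has less power for 50 vs 40 if the gain really is linear: with 0.225 at 50 and 0.45 at 60, n=40 and Bonferroni, about 19% to 20% (noncentrality 0.225·√40 = 1.42) against about 72% for the slope. The planned contrasts already carry that cost, and 60 vs 40 loses almost nothing.
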